## Abstract

**Introduction:**

Achilles tendinopathy (AT) is a cause of pain and disability affecting both athletes and sedentary individuals. More than 150 000 people in the UK every year suffer from AT.

While there is much preclinical work on the use of stem cells in tendon pathology, there is a scarcity of clinical data looking at the use of mesenchymal stem cells to treat tendon disease and there does not appear to be any studies of the use of autologous cultured mesenchymal stem cells (MSCs) for AT. Our hypothesis is that autologous culture expanded MSCs implanted into an area of mid-portion AT will lead to improved pain-free mechanical function. The current paper presents the protocol for a phase IIa clinical study.

**Methods and analysis:**

The presented protocol is for a non-commercial, single-arm, open-label, phase IIa proof-of-concept study. The study will recruit 10 participants and will follow them up for 6 months. Included will be patients aged 18–70 years with chronic mid-portion AT who have failed at least 6 months of non-operative management. Participants will have a bone marrow aspirate collected from the posterior iliac crest under either local or general anaesthetic. MSCs will be isolated and expanded from the bone marrow. Four to 6 weeks after the harvest, participants will undergo implantation of the culture expanded MSCs under local anaesthetic and ultrasound guidance. The primary outcome will be safety as defined by the incidence rate of serious adverse reaction. The secondary outcomes will be efficacy as measured by patient-reported outcome measures and radiological outcome using ultrasound techniques.

**Ethics and dissemination:**

The protocol has been approved by the National Research Ethics Service Committee (London, Harrow; reference 13/LO/1670). Trial findings will be disseminated through peer-reviewed publications and conference presentations.

**Trial registration number:**

NCT02064062.

Strengths and limitations of this studyA first-in-man safety study.First study of its kind injecting culture expanded mesenchymal stem cells into mid-portion Achilles tendinopathy.Capturing both clinical scores and radiological outcomes.Independent assessment using ultrasound tissue characteristics.Proof-of-concept safety study; therefore, further research will be required.

## Introduction

The Achilles tendon is the largest tendon in the body and it plays an important role in the biomechanics of the lower extremity. It can withstand great forces, especially during sporting exercise. The general population has an incidence of 2.35 per 1000 people, equivalent to >150 000 people in the UK every year.^1^

This is a degenerative process that leads to pain and dysfunction in middle-aged individuals and sports participants.^2^ Tendinopathic tendons lose their shiny appearance and microscopy reveals discontinuous and disorganised collagen fibres. This is associated with mucoid and lipoid degeneration and an increasing number of cells within the tendon tissue, mostly with a fibroblastic or myofibroblastic appearance. Often, there is an abrupt discontinuity of both vascular and myofibroblastic proliferation immediately adjacent to the area of greatest abnormality.^3^

Achilles tendon degeneration is evident as an increased signal on MRI^4^ and as hypoechogenic regions on ultrasound investigation.^5^ These areas of abnormal imaging correspond with areas of altered collagen fibre structure and increased interfibrillar ground substance, which has been shown to consist of hydrophilic glycosaminoglycans.^4^

Achilles tendinopathy (AT) adversely affect quality of life by causing chronic pain and disability.^6^ The source of pain has been associated with neurovascular ingrowth and autocrine/paracrine effect of cellular products (eg, catecholamines, acetylcholine, glutamate) and a reduction in pain is a key indicator of treatment success.^3^

Numerous management strategies exist for AT, such as rest, physiotherapy with eccentric strengthening exercises,^7^ extracorporeal shockwave therapy,^8^ dry needling,^8^ high-volume injections^8^ and platelet-rich plasma (PRP) injections.^9^ However, apart from eccentric loading exercises none of these therapies has been shown to be more effective than placebo.^8^
^8^

The use of PRP is controversial. One randomised controlled trial (RCT) looked at PRP versus stromal vascular fraction (SVF) derived from adipose. SVF has been shown to be source of MSCs. They showed that the use of PRP and SVF was safe and that both PRP and SVF improved clinical scores with statistical significance. The use of SVF seemed to provide quicker improvement but at 180 days there was no difference between the two groups.^10^ Another RCT demonstrated that the use of PRP had no statistically significant advantage over a saline placebo group.^9 11^

Although the majority of tendon conditions are treated non-operatively, up to 45% of patients at some stage consider surgery.^3^ Tendon disorders are a major burden on the National Health Service (NHS). A total of 51 454 operations on tendon disorders were performed in the NHS in 2015/2016 (HESOnline), which is up from 48 765 operations performed in 2004/2005. Given that the majority of tendon problems are treated non-operatively, this high surgical caseload represents just the tip of the iceberg of the real cost to the health service of tendon disease. There is therefore a need for safe and effective non-surgical treatments.

Laboratory-based studies looking at autologous mesenchymal stem cells (MSCs) injections into damaged tendons have shown improved functional and histological outcomes.^12–15^ Smith *et al* published an equine case-control trial comparing autologous bone marrow-derived MSCs and saline injections. The treated tendons exhibited statistically significant improvements in key parameters with normalisation of biomechanical, morphological and compositional parameters.^16^ Another study followed up 141 horses postintralesional MSC injection for digital flexor tendinopathy. Two-year follow-up showed no adverse effects of the treatment with no aberrant tissue on histological examination. The re-injury percentage was significantly less than published for national hunt racehorses treated in other ways.^14^

Human studies using MSCs have shown promise in many conditions including heart disease,^17^ musculoskeletal disorders,^18^ autoimmune diseases^19^ and neurological disorders.^20^

With regard to the use of MSCs in human tendons, there are only a handful of reports.

Ellera Gomes *et al*
21 performed a cohort study in 14 patients who received bone marrow concentrate (BMC) derived from the iliac crest with rotator cuff repair. Twelve months following the procedure, all patients had better clinical scores and MRI showed that tendons had healed.

Hernigou *et al*
22 performed a comparative study looking at effect of BMC cells on rotator cuff healing postarthroscopic repair. Patients treated with BMC had a significantly increased healing rate and a significant reduction in rerupture. In contrast, Mazzocca *et al*
23 used BMCs from the humeral head with a similar model of rotator cuff repair, and showed no statistical difference in clinical outcome at a mean of 10.6 months.

Pascual-Garrido *et al*
24 looked at eight patients with patella tendinopathy. BMCs from the iliac crest were injected into the patella tendon under ultrasound guidance. At a mean follow-up of 5 years, there was significant improvement in most clinical scores. This improvement was seen up to year 2 after which it plateaued. Ultrasound evaluation was at 6 months, which showed that eight of the nine patients had improvement in the grading of the patella tendinopathy.

Singh *et al*
25 looked at 30 patients with untreated tennis elbow. BMCs from iliac crest were injected into the lateral epicondyle. There was a statistically significant improvement in the patient-rated tennis elbow evaluation score at 12 weeks.

All of these studies used mononuclear cells from bone marrow concentrate. Usuelli *et al* published a study looking at PRP and SVF. The study concluded that SVF was safe and as efficacious as PRP at 180 days, although this study did not use culture expanded MSCs.^10^ We could only identify one study looking at culture expanded MSCs in AT. Ilić *et al* reported the use of human placenta-derived allogenic MSCs injected under ultrasound guidance in six patients. They monitored for the primary outcome, which was safety. They concluded it was safe to inject human placenta-derived MSCs into human Achilles tendons, however made no comment on clinical outcome.^26^

There is clearly a lack of reliable evidence for the use of MSCs in tendon disease. Our hypothesis is that autologous culture expanded MSCs implanted into a tendon with AT will lead to improvement in pain-free mechanical function. The current paper presents the protocol for phase IIa trial to explore this.

## Methods and analysis

### Study design

Following dialogue and engagement with the Medicines and Healthcare Regulatory Agency (MHRA), the trial was defined as a non-commercial, single-arm, open-label, phase IIa proof-of-concept study. The study will be conducted at the Royal National Orthopaedic Hospital (RNOH). The study will recruit 10 participants and will follow them up for 6 months (figure 1). The MHRA considered this study to be a first-in-man (phase IIa) study whose primary role was to demonstrate safety and hence all patients were to get the active treatment and no control group was used. The information from this study would then be used to design a subsequent phase III RCT involving a control.

**Figure 1 F1:**
[figure not shown]
Trial flow diagram. AT, Achilles tendinopathy; EQ-5D-5L, EuroQol 5-dimension 5-level; GMP, good medical practice; MOXFQ, Manchester Oxford Foot and Ankle Questionnaire; NHS, National Health Service; SAS, Sporting Activity Score; UTC, ultrasound tissue characteristics; VAS, Visual Analogue Score; VISA-A, Victorian Institute of Sports Assessment Achilles Questionnaire.

The primary outcome will be safety as defined by the incidence rate of serious adverse reaction (SAR). The secondary outcomes will be efficacy as measured by patient-reported outcome measures. Ultrasound techniques will assess the radiological outcome of the procedure. Computerised ‘ultrasound tissue characterisation’ (UTC) is also carried out in order to add in a less subjective assessment. UTC involves a precision instrument that moves the ultrasound probe automatically across the long axis of the Achilles tendon collecting transverse images at even distances of 0.2 mm over a length of 12 cm and enable tomographic visualisation and tissue characterisation and quantification of architecture and integrity of the collagenous matrix.

Ultrasound examinations undertaken in this study will performed by a musculoskeletal radiologist with experience of undertaking such an examinations. The end of the Autologous Stem Cells in Achilles Tendinopathy (ASCAT) trial is the last visit of the last participant.

### Inclusion criteria

Patients aged 18–70 years (both males and females) with chronic mid-portion AT (defined by pain and tender swelling in mid-portion of AT, >1 cm proximal to the insertion), with symptoms for longer than 6 months who have failed conservative treatment (at least a full course of physiotherapy) and for whom surgery is being considered. All participants must be able to provide written informed consent. Females of childbearing age and potential must be willing to use two forms of effective contraception from the time of consent to 6 months postinjection (box 1).Box 1Inclusion and exclusion criteria for the studyInclusion criteria:Aged ≥18 and ≤70 years (both males and females).Participants with chronic mid-portion Achilles tendinopathy (AT) (as defined by pain in region of AT and tender swelling in mid-portion of the AT with symptoms for longer than 6 months who have failed conservative treatment (at least a full course of physiotherapy) and for whom surgery is being considered.Able to provide written informed consent.Females of childbearing age and potential must be willing to use two forms of effective contraception from the time of consent to 6 months postinjection.Exclusion criteria:Previous bony surgery (eg, reconstructive pelvic osteotomy) at or in proximity to the bone marrow harvest site.Pregnancy or lactation (self-declaration at screening visit with follow-up urine pregnancy test to be confirmed not beyond 7 days prior to mesenchymal stem cell (MSC) harvest and administration).Current use of steroids, antitumour necrosis factor drugs, methotrexate or ciprofloxacin (or use within 4 weeks of assessment for eligibility).Positive for hepatitis B virus, hepatitis C virus, HIV-1 and HIV-2, syphilis and human T-cell lymphotropic virus.Previous AT surgery on the tendon to receive MSC implantation.Inflammatory arthritis.Known or suspected underlying haematological malignancy.Other active malignancy in the past 3 years.Bovine or antibiotic allergy (since these are in the culture medium).

### Recruitment and consent

Patients who are referred to the RNOH will be identified as potentially eligible for the trial by the Chief Investigator (CI) or delegated clinician and invited to participate. The RNOH is a tertiary referral centre for AT and potential participants will be referred by letter to the Foot and Ankle Department at the RNOH. The CI or delegated clinicians at the Foot and Ankle Department will review referral letters. In the main, it may not be possible to identify relevant patients with chronic mid-portion AT from the referral letters; however, Patient Information Sheets may be sent by post or email to referred patients informing them of the trial. The CI or delegate will wait until the patient is seen in the initial outpatient consultation to explain the trial in more detail and if they are eligible invite them to participate. Participant Identification Centres (PIC) will also be used to identify potential patients for the trial and these may include primary care musculoskeletal triage services. Potential participants will be referred by the PIC to the trial site.

### Screening assessments

Prescreening interview will include a medical history with discussion about willingness to participate in the trial. This will be followed by a clinical assessment that will include a routine examination of the foot and ankle, including: inspection of limb alignment and other biomechanical abnormality such as flat or high arched feet; size and location of swelling over the Achilles tendon and range of motion of the ankles, hindfeet, midfeet and forefeet. Assessment of gastrocnemius tightness will be performed with the knee fully straight and flexed 20 degrees (Silfverskiold test). Examination will aim to rule out other conditions such as an adjacent bursitis or insertional tendinopathy (tenderness over the calcaneal bony attachment). The Simmonds’ test will be performed to ensure continuity of the tendon.

Blood tests will be performed to ensure compliance with the Human Tissue (Quality and Safety for Human Application) Regulations 2007 and local procedures. The minimum blood tests required as specified by the regulations will be hepatitis B virus, hepatitis C virus, HIV-1 and HIV-2, syphilis and human T-cell lymphotropic virus. These tests will be carried out at least 1 week before (and within 30 days of the bone marrow harvest procedure) in line with the regulations. Additionally, a pregnancy test will be carried out prior to the bone marrow harvest (within 1 week), if the participant is a female of childbearing age and potential. If any of these tests are positive, the participant will be counselled and deemed ineligible for the trial.

### Baseline assessment

Baseline assessments to be carried out on day 0, immediately prior to harvest include:Clinical assessment;Baseline questionnaire on demographics and comorbidity/concomitant medication;Victorian Institute of Sports Assessment Achilles (VISA-A) Questionnaire;Visual Analogue Score (VAS);Manchester Oxford Foot and Ankle Questionnaire (MOXFQ);EuroQol 5-dimension 5-level (EQ-5D-5L) Questionnaire;Sporting Activity Score (SAS);Ultrasound imaging and UTC;Adverts events (AE) review.

Table 1 shows all the planned assessments and procedures that will be performed before MSC implantation.

**Table 1 T1:** Schedule for assessments

	Screening	Bone marrow harvest*	Baseline (immediately before implantation)	Implantation	Follow-up			
Visit number	1	2	3		4	5	6	7
Timing postimplantation		Approximate week: 5	Day 0		Day 2†	Week 6	Week 12	Week 24
Deviation window (days)	‡	±14	0		0 hours	±7	±7	±7
Eligibility review	X		X					
Medical history	X							
Informed consent	X							
Clinical assessment	X		X					
HBV, HCV, HIV-1 and HIV-2 and syphilis tests	X							
Pregnancy tests	X§	X	X¶					
Bone marrow harvest		X						
MSC implantation				X				
Routine course of physiotherapy						X**	X**	X**
Ultrasound imaging (conventional ultrasound and UTC)			X**			X††	X††	X††
VISA-A Questionnaire			X			X	X	X
VAS			X			X	X	X
MOXFQ			X			X	X	X
EQ-5D Questionnaire			X			X	X	X
SAS Questionnaire		X						X
Concomitant medication	X	X	X	X	X	X	X	X
AE review		X	X X		X	X	X	X

*Urine pregnancy test at bone marrow harvest.

†Day 2 follow-up assessments are done by telephone.

‡Screening procedures must take place at least 1 week before and within 30 days of the bone marrow procedure.

§Self-declaration from the patient.

¶Within 7 days of implantation.

**The number of visits are dependent on participant’s progress and are not obligatory at these time points. Standard NHS protocol for physiotherapy will start within 1–2 weeks after implantation. Dates of physiotherapy attendances will be recorded in the case report form.

††Two radiologists will independently scan the participant using ultrasound. UTC will also be measured twice on each occasion.

AE, adverse events; EQ-5D-5L, EuroQol 5-dimension 5-level; HBV, hepatitis B virus; HCV, hepatitis C virus; MOXFQ, Manchester Oxford Foot and Ankle Questionnaire; SAS, Sporting Activity Score; UTC, ultrasound tissue characteristics; VAS, Visual Analogue Score; VISA-A, Victorian Institute of Sports Assessment Achilles Questionnaire.

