### Treatment procedure

For eligible participants, approximately 8 mL of bone marrow aspirate will be collected from the posterior iliac crest into a heparinised syringe under either local or general anaesthetic. A decision on which technique will be used will depend on discussions with the patient. MSC processing and manufacturing will be at the cell-processing centre at the Centre for Cell Gene and Tissue Therapeutics based at the Royal Free Hospital in London. The cells are cultured using a standardised protocol using fetal calf serum in the culture medium with robust validation systems to confirm quality and sterility of cells. Approximately 5 weeks after bone marrow harvest, participants will undergo implantation of the culture expanded MSCs under local anaesthetic in the outpatient setting following clinical assessment and tendon imaging using conventional ultrasound and UTC measurement.^27^

A single injection of between 4 and 20×10^6^ MSCs suspended in 1 mL of Dulbecco’s Modified Eagle Medium will be injected under ultrasound control by a delegated, experienced and trained radiologist along the length of the tendon at the area of greatest degeneration starting just distal to the degeneration and finishing just proximal to normal structure. Participants will be observed for a minimum of 2 hours after implantation for any immediate adverse effects.

All participants will be referred for a standard course of physiotherapy. The physiotherapist will issue a discharge summary following their treatment and a copy of this will be included in the participant record. This summary includes details on participant compliance.

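### Text and Table 1 place baseline at different visits, and Table 1 starts the SAS change score about 5 weeks before the other four

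*Protocol article*

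**What the plan says.** In the Baseline assessment section, the sentence that opens the list reads "Baseline assessments to be carried out on day 0, immediately prior to harvest include". The list covers VISA-A, VAS, MOXFQ, EQ-5D-5L, SAS, and ultrasound with UTC.

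Table 1, in the same section, has a different structure. Harvest is visit 2, timed at "Approximate week: 5" with a window of ±14 days. Day 0 belongs only to visit 3, headed "Baseline (immediately before implantation". VISA-A, VAS, MOXFQ and EQ-5D are marked at visit 3 and at weeks 6, 12 and 24. The row labelled "SAS Questionnaire" is marked at harvest and at week 24 only.

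On the gap between the two visits, Treatment procedure says "Approximately 5 weeks after bone marrow harvest, participants will undergo implantation of the culture expanded MSCs", and the abstract says "Four to 6 weeks after the harvest, participants will undergo implantation".

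Subsequent assessments lists SAS with the other scores and places the whole list at 6, 12 and 24 weeks after implantation. Statistical analysis then summarises change from baseline for all five scores and does not say which visit supplies the baseline.

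**The concern.** Harvest and implantation are weeks apart, so one Day 0 cannot precede both immediately. The choice matters because Study design provides no control group: for the efficacy scores, a participant's own baseline is the only comparator. A baseline taken before harvest puts into the change score several weeks in which no cells have been given, together with a marrow harvest under local or general anaesthetic. A baseline taken at implantation does not.

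Under Table 1 as printed, the five scores do not even share a starting point. SAS starts at harvest and the other four at implantation, yet Statistical analysis reports them together as changes from baseline. Staff who follow the text would take every score before harvest; staff who follow the table would do so for SAS alone. A score not collected before implantation cannot be recovered later.

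**Working it through.** The plan states no length for the change-score interval, so there is no figure of its own to reproduce. The check is a reading of the schedule followed by simple arithmetic.

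**Step 1: which visit is Day 0?**

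| Source | Where it puts baseline |
|---|---|
| Baseline assessment, text | Day 0, before harvest |
| Table 1, column heading | Day 0, before implantation; harvest is an earlier visit |
| Sentence introducing Table 1 | "Table 1 shows all the planned assessments and procedures that will be performed before MSC implantation" |
| Treatment procedure | Implantation takes place "following clinical assessment and tendon imaging using conventional ultrasound and UTC measurement" |

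Three of the four point to implantation. For VISA-A, VAS, MOXFQ, EQ-5D and imaging, the table agrees with them, so harvest in the text is most likely a wrong word.

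**Step 2: does that correction settle SAS?** The SAS row has a label and eight visit cells, as does the VISA-A row, so no cell was lost in reading the table. The SAS marks fall in cell 2 (harvest) and cell 8 (week 24). Cell 3 (Day 0 baseline) is empty.

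- If the text is corrected to implantation, it puts SAS at Day 0 and the table puts it at harvest: a conflict on SAS.
- If the text is kept as written, SAS agrees, but the other four scores and the imaging conflict.

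Neither reading reconciles text and table.

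**Step 3: length of the SAS interval under Table 1.** Harvest precedes implantation, so the week 5 in its column is taken as 5 weeks before Day 0. With L the weeks from harvest to implantation, the SAS interval at the last visit is L + 24, and the share before treatment is L / (L + 24).

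| L (weeks) | Source | SAS interval (weeks) | Share before treatment |
|---|---|---|---|
| 5 | Treatment procedure; Table 1 | 5 + 24 = 29 | 5/29 = 17.2% |
| 4 to 6 | Abstract | 28 to 30 | 4/28 = 14.3% to 6/30 = 20.0% |
| 3 to 7 | Table 1, 5 weeks ± 14 days | 27 to 31 | 3/27 = 11.1% to 7/31 = 22.6% |

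The other four scores span 24 weeks. Adding the ±7-day window at week 24 widens the SAS interval to 26 to 32 weeks (3 + 23 to 7 + 25) and the others to 23 to 25 weeks.

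**Step 4: SAS follow-up.** Subsequent assessments gives weeks 6, 12 and 24. Table 1 gives week 24 only. These differ at two visits.

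**The case against.** The strongest reply is that this is editorial. The word harvest is a slip that the same section lets a reader correct, and the SAS anomaly then rests on one mark in one row of a table with other visible irregularities: a doubled mark in an adverse-event cell, and a physiotherapy footnote on the baseline ultrasound. The follow-up sentence refers to Table 1 and reads as a loose summary, since it also lists clinical assessment, which the table marks at no follow-up visit. SAS is a secondary score, described in 10 participants with no test or decision rule. These are people with symptoms for over 6 months who have failed conservative treatment, and nothing shows that SAS moves in 5 weeks. The 17% is a share of time, not of effect.

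Much of this stands. The slip reading is accepted for four scores and imaging, the SAS mark may well be misplaced, and the size of any pre-treatment change is unknown. The mismatch of 29 against 24 weeks arises only under the table; read literally, the text gives all five scores the same pre-harvest start.

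The need for correction remains. A misplaced mark in the assessment schedule still directs when a questionnaire is given, and no reading makes text and table agree on SAS. Nor is this detail that an article leaves to the full protocol: the article prints both versions.

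**Conclusion.** The concern holds. The article contradicts itself on the visit that supplies baseline, on where baseline SAS is taken, and on when SAS is repeated. If Table 1 is followed, SAS change covers nominally 29 weeks and the other four scores 24, with about 17% of the SAS interval before treatment (11% to 23% across the harvest window). This rests on harvest falling about 5 weeks before implantation, as Treatment procedure states, and on the SAS row as printed. How far SAS would change in those weeks cannot be obtained from the document.

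The effect is confined to secondary descriptive summaries. The primary outcome of serious adverse reactions, eligibility and the sample size are untouched. It should be corrected all the same, because change from baseline is the only efficacy contrast in this single-arm study.

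**What to change.** 1. In Baseline assessment, place day 0 immediately before implantation. This changes one word.
2. In Table 1, move the SAS mark from the harvest column to the Day 0 baseline column. This moves one questionnaire to a visit already held. If a pre-harvest SAS was intended, keep it as an extra reading, say so, and still take SAS at Day 0 for the change score.
3. Make Subsequent assessments and Table 1 agree on SAS follow-up. Limiting the text to week 24 costs nothing. Marking weeks 6 and 12 in the table adds one questionnaire at each of two visits already held.

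With these changes, all five change scores at the last visit span 24 weeks (23 to 25 with the visit window).
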